#### Definition

The clinical criteria according to the third international consensus (Sepsis-3) (17):

Sepsis: suspected or documented infection and an acute increase of ≥2 SOFA points.

Suspected infection group will be identified as those who had body fluids sampled for culture and received antibiotics but had a negative culture result.

The documented infection group will be identified as those who had body fluids sampled for culture with a positive result.

Survivors: Patients that survive for 28 days or more after surgery.

Non-survivors: Patients that survive <28 days after surgery.

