### Study Population

The inclusion criteria are the following. Patients between 18 and 85 years of age who will undergo extracorporeal circulation during cardiac surgery, will be admitted to the ICU and provide written informed consent. The control group will be 30 healthy persons aged between 18 and 85 without digestive disease. The exclusion criteria are as follows; patients would be excluded if they (1) had a fever before surgery, regardless of the etiological evidence of infection; (2) had anti-infective treatment before surgery; (3) had gastrointestinal surgery that left the digestive system dysfunctional; (4) had a history of CPB in the last 6 months; or (5) rejected or abandoned ICU therapeutic intervention. The control group will be excluded if they are taking certain medications.

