#### Sample Collection

There will be 60 patients enrolled as the case group and 30 healthy people as the control. After fasting for at least 6 h but not more than 10 h, venous blood will be collected by direct venepuncture or established venous access from patients enrolled. Plasma will be taken from the blood and remain in Eppendorf tubes at −80°C for 1 h. Fresh fecal samples will be obtained (sometimes aided by glycerinum) and stored at −80°C before analysis. In the control group, samples will be collected once. In the case group, feces and blood samples will be acquired at the following time points (Figure 1): (1) T1: 1 day before cardiac operation; and (2) T2: within 24–72 h of ICU admission, sampling must be performed before patients start oral feeding.

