#### Observation and Data Recording

Demographic data describing age, sex, main diagnosis, and past medical history are available at the inception of the study. Data related to the CPB time and application of antibiotics post-operation are available on the MUL-GM-CSCPB study Data Recording Sheet (Supplementary Table). The following observational data will be measured and recorded when patients are admitted to the ICU and at every sampling time.

Sequential (sepsis-related) organ failure assessment includes blood pressure; mean arterial pressure (MAP); and vasoactive drugs, including noradrenaline (NE), epinephrine (E), and dopamine (Dopa); PaO_2_/FIO_2_; Glasgow Coma Scale score; creatinine or urine output; bilirubin; and platelet count.Infection-related items include body temperature, WBC count, neutrophils, PCT, and antibiotics.Whether to be diagnosed with sepsis (according to Sepsis 3.0).Infection site and pathogenic microorganism.Nutrition and gastrointestinal function assessment including enteral or parenteral nutrition, bowel dilatation tested by ultrasound, gastric residual volume and intra-abdominal pressure measured via bladder.

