The current view suggests that intestinal bacteria may lead to sepsis in several ways. First, intestinal bacteria and bacterial products are transferred to distant organs through blood flow. However, this view lacks bacteraemic evidence. Second, intestinal bacterial metabolic products are transferred to distant organs through the lymphatic pipeline. Third, in critically ill patients, changes in the intestinal flora and metabolites can cause systemic inflammatory reactions and the body's immune response, leading to sepsis (26). We suspect that intestinal dysbacteriosis after CPB is a possible mechanism of inflammation and anti-inflammatory immune imbalance, and that bacterial translocation leads to infection and sepsis. In the critical care unit, most common clinical interventions [e.g., enteral feeding (28), proton-pump inhibitors (29), systemic catecholamines (28), and systemic antibiotics (30)] will change intestinal bacteria. It was recently shown that exposure to broader-spectrum antibiotics during hospitalization is associated with dose-dependent increases in the risk of subsequent sepsis (31). Moreover, in critically ill patients, a significant decrease in bacterial diversity was observed. In more than 30% of patients, a single bacterial genus makes up >50% of the gut microbiota (32). Furthermore, in many cases of prolonged critical illness, only two-member pathogen communities remain. The communities contain bacteria associated with the genera Enterococcus and Staphylococcus, and the family Enterobacteriaceae comprises the majority of these communities (33).

Several studies have shown that the role of inflammation in heart failure may promote the gut microbiota as a cardio-metabolic target for intervention (34). The gut microbiota can secrete large amounts of amyloids and lipopolysaccharides, which might produce some proinflammatory cytokines, such as tumor necrosis factor (TNF) (35). TNF could reduce mitochondrial activity, alter calcium homeostasis, and impair β-adrenergic signaling in cardiomyocytes to act as a suppressor of cardiac function (36). It can be seen that the study of intestinal microecology is of great significance for the postoperative inflammation response or sepsis and cardiac function. Therefore, we are reasonably confident that intestinal flora research can be an important breakthrough in the study of the pathogenesis of postoperative sepsis. Differences in species of the intestinal flora also affect the prognosis of sepsis.

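### Where antibiotic exposure before T2 differs between groups, the sepsis versus non-sepsis flora contrast mixes sepsis with its treatment, and the analysis plan does not commit to separating them

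*Protocol article*

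**What the plan says.** The grouping rule in the Definition section is "Sepsis: suspected or documented infection and an acute increase of ≥2 SOFA points". The infection element has two forms:

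- Suspected: "Suspected infection group will be identified as those who had body fluids sampled for culture and received antibiotics but had a negative culture result".
- Documented: "The documented infection group will be identified as those who had body fluids sampled for culture with a positive result". Antibiotics are not a condition here.

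The post-operative sample is defined in Sample Collection as "T2: within 24–72 h of ICU admission, sampling must be performed before patients start oral feeding". Its only ordering rule concerns feeding. Nothing ties it to the start of antibiotics or the onset of sepsis.

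The Discussion lists ICU interventions that affect the flora, ending with "and systemic antibiotics (30)] will change intestinal bacteria".

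Two provisions bear on control of this exposure. Study Population excludes patients who "had anti-infective treatment before surgery", which protects T1 but not T2. Observation and Data Recording states "Data related to the CPB time and application of antibiotics post-operation are available", and also lists antibiotics among the infection-related items recorded at ICU admission and at every sampling time.

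The Multi-Omic Data Analysis Plan names the sepsis versus non-sepsis comparison without specifying a time point. Its mixed model is stated for case versus control. Its logistic regression covers an unlisted set of factors. Antibiotics are neither named nor ruled out.

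**The concern.** The protocol asks whether flora changes after CPB are related to sepsis. By its own account, antibiotics change the flora. On the culture-negative route, a patient cannot be labelled septic without having received them. If many sepsis patients were treated before the T2 stool and fewer non-sepsis patients were, a taxon reduced by the drugs would differ between the groups even if sepsis had no relation to the flora. That difference could be selected as a biomarker, pass into the ROC analysis and be read as support for a gut origin of sepsis.

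The T1-to-T2 change has the same weakness, because T2 is one of its two terms.

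**Working it through.** **No figure to reproduce.** The protocol states no effect size, SD or power for this contrast. What follows shows how a gap in exposure would act. It does not estimate the bias in this study.

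**From the protocol:** 30 sepsis and 30 non-sepsis patients (Study Design); two-sided 0.05 (Multi-Omic Data Analysis Plan).

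**Assumed, because the documents give no values:**
- pS and p0: shares given antibiotics before T2 in the sepsis and non-sepsis groups
- d: antibiotic effect on one flora measure, in within-group SDs
- no true sepsis effect

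**Formulas** (normal approximation):
- Spurious difference = d × (pS − p0)
- Variance in a group with exposed share p = 1 + d² × p(1 − p)
- SE = √[(vS + v0)/30]
- Chance of p < 0.05 = Φ(difference/SE − 1.96) + Φ(−difference/SE − 1.96)

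**One case in full:** pS = 1.00, p0 = 0.50, d = 1.0.
- Difference = 1.0 × 0.50 = 0.50 SD
- vS = 1; v0 = 1 + 0.25 = 1.25
- SE = √(2.25/30) = 0.274
- 0.50/0.274 = 1.83; Φ(1.83 − 1.96) ≈ 0.45, and the other tail is negligible

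**Range** (spurious difference in SD; chance of p < 0.05 on one measure):

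| pS | p0 | d = 0.5 | d = 0.8 | d = 1.0 |
|---|---|---|---|---|
| 1.00 | 0.25 | 0.375; 30% | 0.60; 62% | 0.75; 79% |
| 1.00 | 0.50 | 0.25; 16% | 0.40; 32% | 0.50; 45% |
| 0.75 | 0.25 | 0.25; 16% | 0.40; 31% | 0.50; 43% |
| 0.75 | 0.50 | 0.125; 8% | 0.20; 11% | 0.25; 14% |
| 0.50 | 0.50 | 0; 5% | 0; 5% | 0; 5% |
| 0.50 | 0.75 | −0.125; 8% | −0.20; 11% | −0.25; 14% |

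For scale, 30 versus 30 detects (1.96 + 0.84) × √(2/30) = 0.72 SD with 80% power.

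The bias follows the exposure gap. It vanishes when the shares are equal and changes sign when non-sepsis patients are the more exposed. The T1-to-T2 change carries the same mean shift, d × (pS − p0), because T1 precedes the exposure. Its rejection rates would differ, since the SD of a change is not the SD at T2.

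**Room for adjustment.** No suspected-infection sepsis patient is untreated, so for that subgroup a model can separate drug from sepsis only through treated non-sepsis patients. There would be 0.50 × 30 = 15 of them at p0 = 0.50, and 7 or 8 at p0 = 0.25 (0.25 × 30 = 7.5).

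**The case against.** A reader might infer that antibiotics define the sepsis group, so that the T2 contrast is largely a treatment contrast. The documents do not support this:

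- The documented-infection route needs only a positive culture, and Grouping by Outcomes keeps the two routes apart as subgroups.
- Nothing bars non-sepsis patients from receiving antibiotics.
- Under End Point, observation can run to 28 days, so sepsis and its treatment may begin after T2. Antibiotics started later cannot alter that stool.

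A reader might also quote a very high false-positive rate. With every sepsis patient exposed, 20% of non-sepsis patients exposed and a 1.5 SD effect, it is 98%. All three inputs are assumptions, and no documented figure supports them.

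Nor can it be said that the plan gives antibiotics no role or analyses only T2. The logistic regression's unlisted factors may include them, and the group comparison names no time point. A condensed article may leave a covariate list to a fuller document, and sepsis versus non-sepsis is formally a secondary comparison.

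These arguments limit the claim without removing it. The conflict is within the text shown: one group label contains a drug exposure, the sampling window allows that exposure first, and the protocol says the exposure changes what is measured. The analysis section commits to nothing that deals with it. Although the comparison is listed as secondary, the abstract makes sepsis the question of the study.

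**Conclusion.** The point holds in conditional form and should be fixed. The unadjusted T2 and T1-to-T2 sepsis contrasts mix sepsis with its treatment to the extent that antibiotic exposure before T2 differs between groups. If exposure is equal, the bias is zero.

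Its size cannot be computed from the documents. Over the assumed cases tabulated, the chance of a false finding on one measure runs from 5% to 79%. This depends wholly on the exposure gap and the drug effect, and assumes that exposure precedes T2. The qualitative conclusion rests only on the protocol's own definition, sampling window and statement about antibiotics.

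**What to change.** In the Multi-Omic Data Analysis Plan:

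1. Pre-specify antibiotic exposure before T2 as a covariate or stratification factor in the T2 and T1-to-T2 sepsis contrasts, at whatever level of detail the recording sheet captures. The sheet is a supplement not shown here, so whether it holds class, duration and start time relative to T2 should be checked first.
2. Add a sensitivity analysis among patients with the same antibiotic status at T2, and report suspected and documented infection separately.
3. Report the T1 sepsis versus non-sepsis contrast as the one free of treatment, for any claim that flora precedes sepsis. T1 comes before CPB, so it complements the post-CPB contrast and cannot replace it.
4. Describe the unadjusted T2 difference as reflecting sepsis and its treatment.

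The cost is small. Antibiotic use is already recorded and T1 is already collected, so no new patients or samples are needed and care does not change. The price is lower precision, because exposure and sepsis are likely to be correlated, and limited overlap in culture-negative sepsis, where nobody is untreated. The equal-status subset may be small and should be reported with its numbers.

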## Method and Analysis

### Study Design

This protocol is designed as a prospective observational case–control study in patients who underwent cardiopulmonary bypass (CPB) due to cardiac surgery. Thirty healthy persons aged between 18 and 85, without digestive system disease, will be selected as the control group. The case group will include patients admitted to the intensive care unit (ICU) after cardiac surgery with CPB, which is performed by the Department of Cardiac Surgery of Peking Union Medical College Hospital. The patients enrolled should be divided into two groups according to their outcomes: one group of non-sepsis patients and the other group of sepsis patients after cardiac surgery. Sample collection will be terminated when each group receives 30 cases. These 60 cases will be regarded as the case group. Additionally, all the patients we observe will be further divided into survivors and non-survivors based on 28-days survival. Feces and blood samples will be obtained at certain time points (Figure 1).

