#### Grouping by Outcomes

The primary outcome is patients with cardiovascular surgery with CPB and healthy people.

The secondary outcomes are as follows.

After sample collection, the case group will be selected and divided into two groups according to their clinical outcomes.

Sepsis group (sub grouped by suspected or documented infection) and non-sepsis group;Survivors and non-survivors based on the 28-days survival.

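### The documented-infection rule accepts any positive body-fluid culture, so an untreated coloniser or contaminant plus a SOFA rise of 2 or more is classed as documented sepsis

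*Protocol article*

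**What the plan says.** All of these statements are in the protocol article.

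- **Definition, sepsis:** "Sepsis: suspected or documented infection and an acute increase of ≥2 SOFA points".
- **Definition, suspected infection:** "Suspected infection group will be identified as those who had body fluids sampled for culture and received antibiotics but had a negative culture result".
- **Definition, documented infection:** "The documented infection group will be identified as those who had body fluids sampled for culture with a positive result".
- **Grouping by Outcomes:** the labels form a secondary grouping, "Sepsis group (sub grouped by suspected or documented infection) and non-sepsis group".
- **Study Design:** the group sizes are fixed. "Sample collection will be terminated when each group receives 30 cases".
- **Observation and Data Recording:** antibiotics are listed, as are "Infection site and pathogenic microorganism" and a sepsis diagnosis field that refers to Sepsis 3.0. None of these is made a condition of the documented-infection label.

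**The concern.** The two infection categories ask for different evidence. The suspected category needs treatment and the documented category does not. A positive culture can reflect colonisation (for example of an airway aspirate) or contamination (for example a single blood culture), and the written rule does not separate these from infection. The SOFA condition gives only limited protection. Its components include vasoactive drugs, oxygenation, creatinine and platelets, and the Introduction describes patients after cardiac surgery as usually critically ill.

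The Introduction also says that the study may show whether fever of unknown origin and haemodynamic instability come from sepsis or from inflammation alone. An uninfected patient with inflammatory organ dysfunction and an incidental positive culture is the patient whom that question most needs to keep out of the sepsis group. Any such patient also takes one of 30 fixed places.

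**Working it through.** The article gives no culture, contamination or treatment rates and no power calculation, so there is no stated figure to reproduce. The check has two parts: what the rule does to each kind of patient, and how large the effect could be under stated assumptions.

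**1. The rule applied literally.** Take an uninfected patient who was cultured and has a SOFA rise of at least 2.

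| Culture | Antibiotics received | Label under Definition |
|---|---|---|
| Positive (coloniser or contaminant) | No | Sepsis, documented |
| Negative | No | Non-sepsis |
| Positive (coloniser or contaminant) | Yes | Sepsis, documented |
| Negative | Yes | Sepsis, suspected |

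In the untreated rows the culture result decides between sepsis and non-sepsis. In the treated rows it decides only the subgroup. The documented-infection sentence therefore adds only untreated patients to the sepsis group.

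**2. Size.** All inputs are assumptions except the 30, which is from Study Design:

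- p = proportion with true sepsis: 0.2, 0.3, 0.4
- c = proportion of uninfected patients cultured: 0.3, 0.6
- f = proportion of those with a non-infective positive culture: 0.05, 0.15
- s = proportion with a SOFA rise of at least 2: 0.5, 0.8
- u = proportion of those patients who received no antibiotics: 0.2

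Probability of being added to the sepsis group by this sentence: a = (1 − p) × c × f × s × u. Expected number among 30 labelled septic: 30 × a / (p + a).

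- Smallest (p = 0.4, c = 0.3, f = 0.05, s = 0.5): a = 0.6 × 0.3 × 0.05 × 0.5 × 0.2 = 0.0009; 30 × 0.0009 / 0.4009 = 0.07, about 0.1.
- Middle p, other inputs high (p = 0.3, c = 0.6, f = 0.15, s = 0.8): a = 0.7 × 0.6 × 0.15 × 0.8 × 0.2 = 0.01008; 30 × 0.01008 / 0.31008 = 1.0.
- Largest (p = 0.2, c = 0.6, f = 0.15, s = 0.8): a = 0.8 × 0.6 × 0.15 × 0.8 × 0.2 = 0.01152; 30 × 0.01152 / 0.21152 = 1.6.

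With u = 0.1, the middle-p case becomes 30 × 0.00504 / 0.30504 = 0.5.

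The denominator leaves out treated uninfected patients, whom the article's rules label septic whatever the culture shows. Including them lowers the count. In the middle-p case they contribute 0.7 × 0.6 × 0.8 × 0.8 = 0.2688, which gives 30 × 0.01008 / (0.3 + 0.2688 + 0.01008) = 0.5 instead of 1.0.

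**3. Effect on the contrast.** If the added patients resemble the non-sepsis group, a true difference shrinks by their share of the sepsis group: 0.07/30 = 0.2% at the smallest, 1.0/30 = 3% in the middle-p case and 1.6/30 = 5% at the largest.

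**The case against.** **This is only condensed wording.** The article heads the rules with "The clinical criteria according to the third international consensus (Sepsis-3) (17" and records "Whether to be diagnosed with sepsis (according to Sepsis 3.0", alongside infection site and pathogenic organism. Those fields suggest that cultures get some clinical reading, and a full protocol might say how contaminants are handled. This stands in part: the data for a better rule seem to be collected. However, the article states the grouping rule outright and links none of those fields to it, so this is a rule fixed badly and not a detail left out. The exclusions for preoperative fever and anti-infective treatment do not bear on postoperative colonisation or contamination.

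**Treated patients are labelled septic anyway.** This stands in full and limits the size of the point. A reader might infer that every non-infective positive culture adds a false sepsis case. Without the untreated term, the same assumptions give 0.3 to 6.7 of 30, and 4.3 of 30 (14%) in the middle-p case. The documents do not support that reading. It holds only if no cultured uninfected patient received antibiotics, yet the article plans to record postoperative antibiotic use, so that cannot be presumed.

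**The documented subgroup has no stated special role.** This also stands. A reader might take it as the microbiologically proven end of the sepsis group, but the article does not say so. The analysis plan names no documented versus suspected comparison, and sepsis versus non-sepsis is itself listed as a secondary outcome.

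**Conclusion.** The point holds in a limited form. As written, an untreated patient with a colonised or contaminated culture and a SOFA rise of at least 2 is classed as documented sepsis. A treated patient with the same culture is placed in the documented instead of the suspected subgroup. Nothing elsewhere in the article overrides this.

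The number added to the sepsis group is probably small: about 0.1 to 1.6 of 30, if 20% are untreated and the other inputs lie within the assumed ranges. None of these rates is in the article, so the range is an illustration and not an estimate. A 14% loss of contrast should not be claimed. The movement of treated patients between subgroups may be more frequent, but the documents do not allow it to be sized. The rule is still worth correcting, because the study asks about sepsis as opposed to inflammation alone and the correction is cheap.

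**What to change.** For classification only, and with no bearing on patient care, revise the Definition section as follows:

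- **Documented infection:** a positive culture, with the organism recorded as pathogenic at a recorded infection site, in a patient who received antibiotics.
- **Positive culture judged to be colonisation or contamination:** treat as a negative culture. The patient is then suspected infection if antibiotics were received, and not infected otherwise.
- **Antibiotic condition:** word it identically in both categories. If the documented category alone required antibiotics given for the infection in question, a treated patient with a contaminated culture would become non-septic, while the same patient with a negative culture stayed septic.
- **Timing:** make the judgement before the omics results are seen.
- **Sensitivity analysis:** repeat the sepsis grouping under the any-positive-culture rule.

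The cost is a few sentences, using items that Observation and Data Recording already lists (antibiotics, infection site, pathogenic organism). The list does not mention a separate judgement on colonisation or contamination, and the recording sheet itself is not shown, so that field may have to be added. Slightly fewer patients will qualify as documented, and clinical judgement enters the label. For the 45 case patients reported as already collected under Recruitment, the judgement may have to be made retrospectively.
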